## Abstract

**Background:**

As much as 80% of children on the autism spectrum exhibit challenging behaviors (ie, behaviors dangerous to the self or others, behaviors that interfere with learning and development, and behaviors that interfere with socialization) that can have a devastating impact on personal and family well-being, contribute to teacher burnout, and even require hospitalization. Evidence-based practices to reduce these behaviors emphasize identifying triggers (events or antecedents that lead to challenging behaviors); however, parents and teachers often report that challenging behaviors surface with little warning. Exciting recent advances in biometric sensing and mobile computing technology allow the measurement of momentary emotion dysregulation using physiological indexes.

**Objective:**

We present the framework and protocol for a pilot trial that will test a mobile digital mental health app, the *KeepCalm* app. School-based approaches to managing challenging behaviors in children on the autism spectrum are limited by 3 key factors: children on the autism spectrum often have difficulties in communicating their emotions; it is challenging to implement evidence-based, personalized strategies for individual children in group settings; and it is difficult for teachers to track which strategies are successful for each child. KeepCalm aims to address those barriers by communicating children’s stress to their teachers using physiological signaling (emotion dysregulation detection), supporting the implementation of emotion regulation strategies via smartphone pop-up notifications of top strategies for each child according to their behavior (emotion regulation strategy implementation), and easing the task of tracking outcomes by providing the child’s educational team with a tool to track the most effective emotion regulation strategies for that child based on physiological stress reduction data (emotion regulation strategy evaluation).

**Methods:**

We will test KeepCalm with 20 educational teams of students on the autism spectrum with challenging behaviors (no exclusion based on IQ or speaking ability) in a pilot randomized waitlist-controlled field trial over a 3-month period. We will examine the usability, acceptability, feasibility, and appropriateness of KeepCalm as primary outcomes. Secondary preliminary efficacy outcomes include clinical decision support success, false positives or false negatives of stress alerts, and the reduction of challenging behaviors and emotion dysregulation. We will also examine technical outcomes, including the number of artifacts and the proportion of time children are engaged in high physical movement based on accelerometry data; test the feasibility of our recruitment strategies; and test the response rate and sensitivity to change of our measures, in preparation for a future fully powered large-scale randomized controlled trial.

**Results:**

The pilot trial will begin by September 2023.

**Conclusions:**

Results will provide key data about important aspects of implementing KeepCalm in preschools and elementary schools and will provide preliminary data about its efficacy to reduce challenging behaviors and support emotion regulation in children on the autism spectrum.

**Trial Registration:**

ClinicalTrials.gov NCT05277194; https://www.clinicaltrials.gov/ct2/show/NCT05277194

**International Registered Report Identifier (IRRID):**

PRR1-10.2196/45852

## Introduction

### Background

Children on the autism spectrum can exhibit challenging behaviors, such as aggression, self-injury, and property destruction [1-3], which occur in as much as 80% of children [4]. These behaviors can have a devastating impact, negatively affect personal and family well-being [5], contribute to teacher burnout [6], and even lead to hospitalization [7]. Challenging behaviors may stem from a culmination of physiological and psychosocial stress when children are unable to regulate their stress, that is, when they do not have a repertoire of emotion regulation strategies to call on to defuse their stress [8,9]. Emotion dysregulation—difficulties with monitoring, evaluating, and modifying emotional responses to environmental demands [10]—is thought to serve as a mediator between stress and challenging behaviors in autism [11,12]. Consistent with this notion, recent literature has documented that challenging behaviors in children and adolescents with autism spectrum disorder are more likely to surface in response to situations placing demands that exceed their emotion regulation skills [13]. Individuals on the autism spectrum are more likely to experience stressful events compared with their peers owing to their difficulties with communicating, understanding others’ behaviors, and responding to demands; sensitivities to sensory stimuli; insistence on sameness; and social expectations that might be perceived as emotionally overwhelming [9]. These difficulties or factors can be particularly pronounced in the school setting [14]. Therefore, these difficulties with emotion dysregulation, in addition to frequently experienced stressors, place children on the autism spectrum at high risk for frequent challenging behavior episodes.

Evidence-based strategies for managing challenging behaviors and supporting emotion regulation in schools include proactive (antecedent) and reactive (consequent) strategies [1,15,16]. Proactive strategies, such as setting routines and tailoring the environmental or instructional design to prevent challenging behaviors, are typically preferred to reactive strategies, such as punishment and planned ignoring [1,15,16]. However, even when proactive strategies are well implemented, challenging behaviors still occur, with parents and teachers often reporting that they occur without warning [11,12]. In children on the autism spectrum, triggers can be difficult to determine even with expertise in functional behavioral assessment (which is not standard training for the teaching force) [17], as children on the autism spectrum often have trouble in communicating their stress [18]. Therefore, it is critical to understand the stress-related triggers that lead to the onset of challenging behaviors. Early detection of rising stress can allow for the implementation of proactive strategies targeting stress reduction or emotion regulation, such as emotion regulation training; mindfulness-based strategies; the prompting of cognitive reappraisal; functional communication training; or other antecedent-based strategies, such as providing access to sensory stimuli or offering choices.

A way to know when a child may be experiencing stress before a challenging behavior, and thus intervene early, is by measuring the physiological state; physiological state is a well-recognized index of stress, which may be captured using many physiological channels, including heart rate (HR) [19-24]. Many theoretical frameworks point to a causal pathway between physiological stress and challenging behavior [8,25-27], and previous studies have shown elevated HR before the onset of a challenging behavior in adults on the autism spectrum [28,29]. In our previous study, we found that there is often a >22% increase in HR in the 58 seconds immediately preceding the challenging behavior and that this increase has moderate utility in predicting challenging behaviors (area under the curve [AUC]=0.72; *P*<.001) [30]. We replicated this finding in 2 samples of children aged 8 to 12 years on the autism spectrum, finding that 33% to 36% increase in HR in the preceding 76 to 80 seconds was associated with challenging behaviors (AUC=0.75-0.82). These results were again replicated in another data set including both children and adolescents on the autism spectrum (AUC=0.71) [31]. These studies suggest that responding to early HR increases may be a more direct approach to identifying the need for emotion regulation strategies, which may support the identification of behavioral triggers.

Timely identification of stress may help prevent emotion dysregulation and challenging behaviors. In addition, children on the autism spectrum may be less equipped to deal with this stress, as many have well-documented difficulties in independently using emotion regulation strategies and instead more frequently rely on maladaptive or ineffective strategies, such as rumination or shutting down [32-37]. Thus, difficulty in emotion regulation is likely a mechanism by which stress contributes to challenging behaviors, and teaching emotion regulation is critical. However, there are 3 barriers that limit the use of emotion regulation strategies for managing challenging behaviors in children on the autism spectrum in school settings. First, teachers may not detect children’s stress-related triggers or their rising stress, with or without training, as children on the autism spectrum often do not express emotions verbally or in clear, observable ways using nonverbal communication channels [18]. Therefore, the detection of stress by teacher’s observation alone may be sometimes ineffective or unreliable.

Second, teachers work in dynamic and fast-paced classroom environments. Even when teachers are sensitive to behavioral triggers and evidence-based behavior plans are in place, teachers have multiple demands on their attention and may not recognize a trigger or recall the best strategies to use with each student in the moment of crisis. In addition, teachers’ own stress during episodes may interfere with this recall, as their stress has been found to interfere with delivery of evidence-based practices in schools [38,39]. Therefore, teachers need support to implement emotion regulation interventions with children on the autism spectrum.

Third, teachers may not have the training or resources to monitor how well the strategies are working. Many teachers do not receive training in program monitoring and analysis that is required to refine children’s behavioral plans, limiting their ability to make data-informed decisions about which strategies work for a given child. Even when teachers have training in outcome measurement and monitoring, they may be unable to systematically monitor the success of strategies owing to competing demands. They may not have the time, personnel, or technological resources to determine which strategies are the most effective. Our proposed mobile health (mHealth) app, KeepCalm, is designed to address these 3 barriers and reduce or prevent challenging behaviors in children on the autism spectrum (Figure 1; app development and features are described in the *Methods* section).

The KeepCalm app is designed as a real-time electronic clinical decision support tool, otherwise known as a *just-in-time adaptive intervention* (JITAI) augmentation, a term coined in mHealth [40]. JITAI augmentations are intervention supports designed to provide the right type or amount of support at the right time by adapting to a person’s changing internal and contextual state (eg, by tracking physiological stress, sleep quality, exercise or activity, temperature, and location). Most JITAI technologies are designed to support the individual client directly (eg, check-in messages and resources for clients with alcohol use disorder, triggered by GPS data showing that they are near a predetermined risk location, such as a local bar) [41]. However, the KeepCalm app is one of the first (also refer to the studies by Juarascio et al [42] and Clausen et al [43]) to support the provider (in this case, teacher or aide) directly, so that they may in turn best support their client (in this case, student).

**Figure 1 figure1:**
[figure not shown]
Barriers and the KeepCalm app’s corresponding proposed innovations to be tested.

### Objectives

We present the framework and protocol for a pilot randomized waitlist-controlled field trial that aims to examine the implementation of a digital mental health app, the KeepCalm app (refer to the *Materials* section for details about the app), designed for children on the autism spectrum with challenging behaviors of any IQ or speaking ability. Given that >95% of digital mental health apps have not actually been studied [44,45], an overarching goal of the project is to test the KeepCalm app systematically. We expect the KeepCalm app to score high on usability, acceptability, feasibility, and appropriateness. We also predict satisfactory proximal efficacy (>80% clinical decision support success rates and <20% false positive and negative rates), high technical reliability (the removal of artifacts and offline mode activation success), and the use of the KeepCalm app to result in low severity and frequency of challenging behaviors and emotional dysregulation in children on the autism spectrum after the trial relative to baseline.

## Methods

### App Development Work

We have used user-centered design [46,47] methods to develop the mHealth KeepCalm app by involving key stakeholders in each phase of development and testing [47-49]. As part of the early stages of the project, we have already conducted needs assessments with school personnel and parents to understand their needs in managing children’s challenging behaviors and supporting their emotional regulation. We are in the process of completing 5 cycles of rapid cycle prototyping (so far, 4 cycles have been completed, including 2 with the live app prototype). App feedback gathered through this testing has directly informed future app iterations. We have also gathered data showing high usability, feasibility, acceptability, and appropriateness of the KeepCalm app and data from associated HR trackers and accelerometry devices to examine in the context of regulatory and ethical educational frameworks [50]. Alongside this work, we conduct expert advisory board meetings with a board composed of relevant experts in the community (the autism support coordinator from the School District of Philadelphia, teachers, teacher coaches, parents, and adults with autism). The board meets every few months to gather their feedback about and support for every aspect of the project, including app features and design, in-app evidence-based strategy resources, study methods, and recruitment. All previous work will inform the final KeepCalm app to be tested in this pilot randomized waitlist-controlled field trial.

### Design

We will conduct a pilot randomized waitlist-controlled field trial of the KeepCalm app (refer to the *Materials* section for details about the KeepCalm app) in which participants will either be randomized to the KeepCalm app for a period of 3 months or will be included in a waitlist and will trial the app for 3 months after an initial 3-month waiting period. In this trial, the KeepCalm app will be tested for usability, feasibility, acceptability, and appropriateness, and we will also collect some preliminary proximal and distal efficacy data to inform a future, fully powered randomized field trial.

### Participants and Recruitment

Overall, 20 educational teams comprising a preschool or elementary school student on the autism spectrum, their parent, their teacher, and their aide (if they have one) will be recruited. If a child does not have an aide or their aide declines to participate, their speech therapist, occupational therapist, or another educational team member may participate instead. Therefore, at a minimum, teacher-child or parent dyads will be consented, with some teams forming a triad with an aide or other member of the educational team. Teachers may participate with 1 to 2 of their students on the autism spectrum.

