### Procedure

The trial is registered at ClinicalTrials.gov (NCT05277194). After screening for eligibility, the 20 teams (at a minimum, teachers-parents and child dyads; at a maximum, teachers-parents and child-aide [or other educational team member] triads) will be randomized to the waitlist (n=10, 50%) or treatment group (n=10, 50%). The treatment (and later, the waitlist) group will use the app for 3 months. After a dyad or triad has signed up for the study, participants will complete a conferencing software-based intake meeting, during which they will be individually briefed about the KeepCalm app and complete the baseline assessments.

School personnel will then complete an in-app training session either remotely or in the classroom, during which they will receive access to the KeepCalm app, HR tracker, and accelerometer. The research team will also show or instruct teachers about how to put the HR tracker and accelerometer on the child or assist or instruct the child in putting them on themselves. Participants will download the app onto their own phones or, if they do not have an iPhone, an iPhone will be lent to them for their participation in the project. A member of the research team will also help the school personnel to customize the app for their student by showing them how to add the child’s profile and their triggers, behaviors and skills, and strategies. Standard but editable lists will be programmed into the app for each student, including evidence-based proactive and reactive strategies for reducing challenging behaviors and supporting emotion regulation [64]. All teachers recruited will have had professional development and in-class coaching in these strategies by coaches in our center. The research team will administer a fidelity assessment tool to teachers to understand their proficiency in implementing these strategies and provide additional coaching or resources for strategies, as needed.

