#### Power

For the study’s pilot randomized controlled trial, the analyses will focus on feasibility, usability, and implementation (descriptive) data but will include some preliminary efficacy inferential analyses. In this study, 50% (10/20) of the teams will be randomized to the treatment condition and 50% (10/20) of the teams will be randomized to the waitlist control condition. The sample size was not based on power analysis but rather a need to obtain pilot data that will support an app for a fully powered trial.

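### Student-based teams are randomized 10:10, but a teacher may enroll two students and no rule keeps them in one arm, so the exploratory waitlist comparison is open to contamination

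*Protocol article*

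**What the plan says.** Participants and Recruitment defines a team as one student with the parent, the teacher and, where there is one, an aide. The same section states: "Teachers may participate with 1 to 2 of their students on the autism spectrum". Two teams can therefore share a teacher.

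The team is the randomized unit. The Power section says that "50% (10/20) of the teams will be randomized to the treatment condition and 50% (10/20) of the teams will be randomized to the waitlist control", and Procedure gives the same 10 and 10. Neither section says that teams with a common teacher are allocated together.

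Under Design, waitlist participants "will trial the app for 3 months after an initial 3-month waiting period". The intervention is delivered to school staff. Procedure says: "School personnel will then complete an in-app training session either remotely or in the classroom". That section also provides extra coaching or resources where a fidelity assessment shows a need.

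Under Measures and in Table 1, teachers alone complete the SSQ, and teachers and parents complete the IBR-MOAS and EDI. Under Secondary Outcomes in Data Analysis, these scales are compared between the two groups at baseline and after the trial by a repeated measures ANOVA, which the article itself calls exploratory and underpowered. No teacher term is named.

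**The concern.** The app acts through the teacher, but allocation follows the child. A teacher with one student in each arm is trained on the app and using it during the very months in which the second student is meant to be without it. Strategy resources, added coaching and experience of what works can pass to the waitlist child. The same teacher also scores both children and necessarily knows which of them wears the tracker.

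Two things are at stake in the distal comparison. The between-arm difference can be biased, and its standard error can be wrong because two ratings by one teacher are not independent. The article wants these pilot data, including the sensitivity of its measures to change, to prepare a fully powered trial, so the errors could carry forward. The Discussion names small sample size as the main limitation and does not mention shared teachers.

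**Working it through.** **Inputs.** From the article: 20 teams, 10 per arm, one or two students per teacher. Not given: the number *k* of two-student teachers, the degree of carry-over and the within-teacher correlation. These are shown as ranges. There is no powered sample size to reproduce, since the article says that 20 was not derived from a power analysis. The only check possible is 10 + 10 = 20, which agrees.

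**One teacher.** Wherever the first student is allocated, 10 of the remaining 19 places lie in the other arm, so P(split) = 10/19 = 0.526.

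**Any of *k* teachers.** Assuming every 10:10 allocation of the 20 teams is equally likely,

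P(no split) = Σ_j C(k, j) × C(20 − 2k, 10 − 2j) / C(20, 10), with C(20, 10) = 184,756.

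For k = 2: (8,008 + 25,740 + 8,008) / 184,756 = 41,756 / 184,756 = 0.226, so P(at least one split) = 0.774.

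The expected number of splits is k × 10/19. Each split exposes one of the 10 waitlist teams, so the expected exposed share is s = k/19.

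| k | Teachers in all (20 − k) | P(at least one split) | Expected splits | Exposed share of waitlist teams |
|---|---|---|---|---|
| 0 | 20 | 0% | 0 | 0% |
| 1 | 19 | 53% | 0.53 | 5% |
| 2 | 18 | 77% | 1.05 | 11% |
| 5 | 15 | 97% | 2.63 | 26% |
| 10 | 10 | 99.9% | 5.26 | 53% |

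The last row requires every teacher to enroll two students.

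**Dilution from carry-over alone.** If a fraction c of the effect reaches an exposed waitlist child, the expected difference is the true difference × (1 − s × c). Taking a true standardized difference of 0.8 and c from 0.25 to 1 (both assumed), it falls to 0.78–0.72 for k = 2, 0.75–0.59 for k = 5 and 0.70–0.38 for k = 10. Full carry-over (c = 1) is an upper bound, not an expectation.

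**Standard error.** Let two ratings by one teacher have variance σ² each and correlation ρ > 0. If the students are in different arms, the variance of the difference is 2σ²(1 − ρ), and an analysis that assumes independence overstates it. If they are in the same arm, the variance of the sum is 2σ²(1 + ρ), and that analysis understates it. The net error depends on the mix of split and unsplit pairs.

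**After the fix.** With randomization by teacher, the chance of a split is 0. The design effect is 1 + (Σm²/20 − 1) × ICC, where m is the number of students per teacher. Since Σm² = 4k + (20 − 2k) = 20 + 2k, this is 1 + (k/10) × ICC. At an assumed ICC of 0.05 to 0.4:

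- k = 2: design effect 1.01–1.08; 20 teams act like 19.8–18.5.
- k = 5: 1.025–1.20; 19.5–16.7.
- k = 10: 1.05–1.40; 19.0–14.3.

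**The case against.** The strongest reply is that little rests on this comparison. The primary outcomes are usability, acceptability, feasibility and appropriateness, analysed descriptively. The technical and proximal outcomes are descriptive too. Objectives words the behavioral expectation as change from baseline, and no decision rule depends on the between-arm contrast. This stands, and it limits the severity. It does not remove the point, because low power is disclosed imprecision whereas contamination is a bias that the article does not mention.

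Second, carry-over may be modest. Procedure says that all recruited teachers already have training and in-class coaching in the strategies. The alerts are calibrated to the individual child's baseline heart rate, and the top strategies are individualized and triggered by that child's stress zone, so neither reaches a waitlist child directly. This also stands: full carry-over is implausible. App resources, added coaching, experience and the shared rater remain.

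Third, a fuller protocol might hold a same-arm rule. That is possible, but the article itself fixes both the unit of randomization and the two-student allowance, and together these permit split teachers.

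Three stronger readings are tempting and are not supported:

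- *The bias must be toward zero.* Carry-over would act that way, but an unblinded teacher scoring a treated and a waiting child side by side could widen the gap.
- *The waitlist arm is certainly contaminated.* With no two-student teachers there is no problem, and their number is not stated.
- *Baseline ratings follow allocation.* Procedure mentions randomization before it describes an intake at which participants are "individually briefed about the KeepCalm app and complete the baseline assessments". But that text is not clearly chronological: it also mentions sign-up after randomization, although sign-up must come first. Nothing says that the arm is known when baseline scores are given.

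**Conclusion.** The point holds as a should-fix. As written, the plan allows one teacher to sit in both arms, and this becomes likely with only a few two-student teachers: the chance passes one half with a single such teacher and three quarters with two. The figures assume simple 10:10 allocation of teams with no restriction on shared teachers, which is what the article describes. The size of any bias cannot be fixed from the documents, because the number of two-student teachers and the degree of carry-over are not given, and its net direction is uncertain. The standard error of an ANOVA without a teacher term can be wrong in either direction. The consequence is confined to the exploratory waitlist-versus-treatment comparison of SSQ, IBR-MOAS and EDI. The rater problem concerns the teacher-completed forms only. An aide or therapist serving two teams would raise the same carry-over issue.

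**What to change.** Randomize by teacher (classroom), so that both students of one teacher, and any staff they share, go to the same arm. Block on one- versus two-student teachers to stay near 10 teams per arm. In the exploratory model, include teacher as a random effect. Cluster-robust standard errors are not a good substitute, because they are unreliable with the 10 to 20 clusters available here.

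The change needs a few sentences in the protocol and a revised allocation list, and it must be made before allocation, since a split teacher cannot be undone afterwards. There are three costs:

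- Arms may be unequal. With 5 two-student teachers, for example, 5 + 2 × 2 = 9 teams against 5 + 3 × 2 = 11.
- There are fewer independent units, by the amounts worked out above. The loss is slight when few teachers have two students, but not negligible if most do.
- A teacher's students should be identified and consented before that teacher is allocated, so that enrollment of the second child does not depend on a known arm.
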